**8) Design**

Study site

The investigation will take place at the KEMRI Centre for Geographic Medicine Research – Coast, Kilifi. There are several dispensaries suitable for such a study in Kilifi district. We currently plan to use Gongoni dispensary, 30km south of KEMRI Centre for Geographic Medicine Research. Kilifi District experiences long rains in May-July and short rains in November/December. Gongoni is near a fresh water lake, and this may explain the continued presentation of malaria cases to Gongoni dispensary when other areas have little malaria. Measured Entomological Inoculation Rates in the area vary from 10-50 per year. The dispensary is the primary source of antimalarial treatment in the area: there are very few shops or private dispensaries in the area. The local administrative structure involves an area chief, a sublocation chief, a dispensary health committee and a clinical officer based in the dispensary. All these parties are keen to facilitate interventional research in the area. Adequate space exists in the dispensary to see children for clinic visits and immunisations.

Study population

There are 600 children between the ages of 1 and 6 years within a 2 kilometre radius of the dispensary. The local population are predominantly Mijikenda (Giriama), and subsistence farmers.

Sampling

A sample size calculation using a time to event, and assuming an even distribution of the risk of malaria, is based on a 60% risk of clinical disease during the first rainy season (estimate from previous studies in the area). To detect 40% efficacy with 90% power at p=0.05 requires 340 children in total, allowing for 30% probability of loss to follow up (spread over the period of monitoring) requires 372 children. To accommodate early loss to follow up, and incomplete immunisations, we aim to recruit 410 children, which we estimate will require 450 children to be screened for eligibility. Should the proportion of children with malaria attributable fever be only 40% because of poor rainfall, we would still have 90% power to detect 48% efficacy.

Sensitisation and recruitment

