###### Exclusion criteria

Exclusion criteria will be:

- Clinically significant skin disorder, allergy, symptomatic immunodeficiency, cardiovascular disease, respiratory disease, endocrine disorder, liver disease, renal disease, gastrointestinal disease, neurological illness, severe malnutrition (mid upper arm circumference less than 11 cm).
- History of splenectomy
- Serum creatinine concentration above the age related normal range in Kilifi.
- Serum ALT concentration above the normal range in Kilifi
- Clinically significant anaemia, (ie. with symptoms of limited exercise capacity, or signs of a high cardiac output state; large volume pulse, heaving cardiac apex beat, resting tachycardia).
- Blood transfusion within one month of the beginning of the study
- History of vaccination with previous experimental malaria vaccines
- Administration of any other vaccine or immunoglobulin within two weeks before vaccination.
- Current participation in another clinical trial, or within 12 weeks of this study
- Any other finding which in the opinion of the investigators would increase the risk of an adverse outcome from participation in the trial.
- Likelihood of travel away from the study area

Urine will be collected for dipstick examination for blood and protein at screening only, to avoid immunising a child with sub-clinical glomerulonephritis. Stool will be collected for microscopy.

*HIV testing*

There is no requirement for host immunity to limit replication of the virus vectors, since they are only capable of a single round of replication *in vivo,* and no reason to suppose particular risk to HIV positive individuals.Indeed, we have now immunised 3 HIV positive adults in Kilifi, and safety data is reassuring for very similar vaccines in HIV positive adults elsewhere. We do not plan to include HIV testing in the screening tests before immunisation, and this is likely to result in 3 children with HIV being immunised. Should a severe adverse event be possibly vaccine related in the view of the Data Safety Monitoring Board, we would request parental consent for HIV testing of the affected child.

Blood sampling

5 mls of blood will be collected at screening, one week after final immunisation and 8 -18 weeks after final immunisation, and at the end of 9 months surveillance. The order of sampling at this latter timepoint will be assigned randomly. The following tests will be performed:

- Full blood count
- Serum ALT and creatinine

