Plasma and cells will be stored at -20C and -192C respectively. *Ex vivo* and cultured ELISpot’s are currently being performed in the immunology laboratory at the CGMRC, Kilifi, and results are validated by rigorous use of negative and positive controls. This technique uses either overnight or prolonged stimulation by antigen of separated lymphocytes from the child’s blood sample to count the number of interferon gamma producing cells. Antibodies against MSP1-19, AMA and red cell variant markers will be measured.

Dissemination and explanation of blood results

All non immunology blood results will be given to and explained to all parents after screening and at follow-up visits. Immunology results will be explained in general terms, for the group not for individuals, at the end of the study. Those with abnormal blood results at screening will be offered appropriate investigations and treatment or referral as necessary. Parents will receive an explanation of all screening results before proceeding with immunisation. We will provide treatment should parents request treatment for symptomless malaria parasitaemia or intestinal helminth infections. Parents of children with symptomless malaria parasitaemia will be warned that they should present for assessment should they develop fever.

2. Vaccine administration

*Randomisation*

Children will be given serial numbers in the order of recruiting. A random allocation order in blocks will be generated by an independent statistician, part of the DSMB, and sent to the local safety monitor. The list of children will be ordered by age and sex, before being given to the local safety monitor. The local safety monitor will then apply the order of the random block allocation to the children in the list given to him/her by the principle investigator.

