***Immunogenicity***

Both ITT and ATP cohorts will be analysed, using both immediate *ex vivo* and cultured ELISpots. Immunogenicity will be examined by age, sex, presence of stool helminth infection and parasitaemia at screening. Geometric means of T cell numbers with 95% confidence intervals for central tendancy will describe groups.

*Demographic data.*

Age, sex and bed net use will be presented by treatment group to ensure comparability.

*Efficacy*

Efficacy will be analysed by both ITT and ATP.

Primary Analysis

Cox regression model analysis of incidence of clinical disease will allow assessment of the time to first episode as the primary outcome. Clinical disease will be defined by fever and parasitaemia above a threshold defined from logistic modelling of the risk of fever for parasite densities. Age, bed net use, blood stage immunity, sickle cell status and thalasaemia typing will be used as covarietes. It will also allow correlation of immune responses with protective efficacy.

Secondary analyses

- The total number of clinical disease episodes during surveillance, using age, bed net use and blood stage immunity as covarietes.
- the number of febrile malaria episodes in vaccine versus control groups, as calculated by the Malaria Attributable Fever Fraction, corrected by number of children and time of observation. This method does not assign a definitive status to each child, but produces a figure for the fraction of the group estimated to have febrile malaria. The cross-sectional bleed will be used to fit the model by providing the afebrile population, but will not be used in determining the Malaria Attributable Fever Fraction. The first half and second half of monitoring will be analysed separately.
- the other secondary analyses will compare mean haemoglobin concentrations during cross-sectional surveys, and the number of high parasitaemia (>500,000 per microlitre) infections in each group. The incidence of severe malaria will not be frequent enough to allow analysis, but data will be presented.

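### The total-episodes analysis drops two covariates of the primary model and the haemoglobin comparison names no baseline adjustment: some precision is given up, validity is not affected

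*Protocol*

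**What the plan says.** All the analyses concerned stand in the protocol, section 9 (Data Management), under Efficacy.

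- **Primary analysis** (Cox regression, time to first episode): "Age, bed net use, blood stage immunity, sickle cell status and thalasaemia typing will be used as covarietes".
- **Secondary, total number of clinical disease episodes:** "using age, bed net use and blood stage immunity as covarietes". The two red-cell traits are absent from this list, and no reason is given.
- **Secondary, haemoglobin:** "the other secondary analyses will compare mean haemoglobin concentrations during cross-sectional surveys". No model and no covariate is named. The section on surveillance (Cross sectional study) places these surveys three months into surveillance and at its end.

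The baseline data exist. Under Blood sampling in section 8, "5 mls of blood will be collected at screening", and the list of tests that follows includes a full blood count and typing for sickle cell and thalassaemia. The Laboratory procedure paragraph confirms that the typing uses the screening sample. The paragraph on anaemia at screening shows that screening haemoglobin is looked at child by child.

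On allocation, the Randomisation paragraph states: "The list of children will be ordered by age and sex".

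**The concern.** Two things stand out.

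First, the primary and total-episodes analyses count the same kind of event, and the null hypothesis in section 6 covers both the rate of development and the number of episodes. By putting sickle cell status and thalassaemia type into the primary model, the protocol treats them as prognostic for clinical malaria. Nothing in the document suggests that they stop being prognostic when all episodes are counted instead of the first. Yet the total-episodes list is written out as a complete list without them.

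Second, the trial enrols children aged 1 to 6 and admits those with anaemia if they have no clinically significant signs or symptoms. Part of the spread in follow-up haemoglobin will therefore have been present before vaccination, and it is already measured. If it is not adjusted for, it stays in the error term.

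What is at stake is the width of the confidence intervals of two secondary comparisons.

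**Working it through.** **The protocol's own figures.** The only stated calculation is for the primary endpoint: "To detect 40% efficacy with 90% power at p=0.05 requires 340 children in total", from a "60% risk of clinical disease during the first rainy season" in controls, and, "allowing for 30% probability of loss to follow up (spread over the period of monitoring) requires 372 children". With a two-sided 0.05 level (sidedness is not stated) and a hazard ratio of 0.60:

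- Schoenfeld's formula gives 162 events. With risks of 60% and 36% (mean 0.48), 162 / 0.48 = 338 children, against 340 stated.
- With efficacy on the hazard and loss at a constant rate to 30%, the mean event probability is 0.440, and 162 / 0.440 = 369 children, against 372 stated.

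Both come within 3%, though under different readings of efficacy. They say nothing about the secondary comparisons, for which no power is stated. They serve here only as a source for the number of children.

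**Covariate sets side by side.**

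| Covariate | Time to first episode | Total episodes | Haemoglobin | Available at screening |
|---|---|---|---|---|
| Age | yes | yes | not named | yes |
| Bed net use | yes | yes | not named | yes |
| Blood stage immunity | yes | yes | not named | timing not needed for this point |
| Sickle cell status | yes | **no** | not named | yes |
| Thalassaemia type | yes | **no** | not named | yes |
| Screening haemoglobin | no | no | **not named** | yes |

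**Size for haemoglobin.** In a linear model, adjusting for a baseline that correlates r with the outcome multiplies the variance of the treatment difference by 1 − r². The protocol gives neither r nor the standard deviation (SD), so both are assumed: r from 0.3 to 0.7, SD 1.0 or 1.5 g/dl. The number per arm is 372 / 2 = 186.

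- Unadjusted, SD 1.0: standard error = 1.0 × √(2/186) = 0.1037 g/dl; 95% half-width = 1.96 × 0.1037 = 0.203 g/dl.
- Adjusted: multiply by √(1 − r²).

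| Assumed r | Variance factor 1 − r² | Variance saved | Equivalent sample size 1/(1 − r²) | Half-width, SD 1.0 | Half-width, SD 1.5 |
|---|---|---|---|---|---|
| 0 (no adjustment) | 1.00 | 0% | 1.00 | 0.203 | 0.305 |
| 0.3 | 0.91 | 9% | 1.10 | 0.194 | 0.291 |
| 0.5 | 0.75 | 25% | 1.33 | 0.176 | 0.264 |
| 0.7 | 0.51 | 49% | 1.96 | 0.145 | 0.218 |

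The proportional saving depends on r alone. With 143 per arm (30% lost from 205) and SD 1.0, the half-width falls from 0.232 to between 0.221 and 0.166 g/dl.

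**Size for episode counts.** The 1 − r² rule is for a continuous outcome in a linear model and does not carry over to counts. The protocol gives neither the frequency of the two traits nor their effect on episodes, and it names no model for the count. No figure can be derived.

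**Size for sex.** A weak covariate explaining an assumed 0.5% to 2% of the variance lowers the standard error by 1 − √0.995 = 0.25% to 1 − √0.98 = 1.0%.

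**The case against.** The strongest reply concerns haemoglobin. The protocol does not say that the means are raw or unadjusted, and ANCOVA also compares means. The section on the Data Safety Monitoring Board foresees a separate reporting and analysis plan, and covariates for a secondary endpoint are often left to such a plan. This stands in part: the text is silent rather than wrong, so the haemoglobin part is a recommendation. The reply does not reach the total-episodes analysis, where the protocol names a list that differs from its own primary list.

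The size of the haemoglobin gain is also open to challenge. Screening fell in February to March 2005 and the last bleed was due in January 2006. In between, the protocol provides iron for low haemoglobin, antimalarials for all children after the third dose, and helminth treatment. All of these could weaken the correlation. This stands, and is why the range starts at r = 0.3, where the gain is small.

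Three stronger readings are tempting, and the documents do not support them.

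- *The two efficacy estimates are not comparable because their covariates differ.* A first-episode hazard ratio and a comparison of total episodes are different quantities under any covariate set. The traits are baseline characteristics, balanced in expectation by randomisation. If total episodes are analysed with a log-link rate model, omitting them leaves the rate ratio itself unchanged.
- *ELISpot should be adjusted for its baseline too.* The Immunogenicity paragraph uses geometric means with intervals to describe the groups. It states no test between arms that could lose precision.
- *Sex must be in every model because it orders the allocation list.* Age, the first ordering variable, is in both episode models. Including sex would respect the design, but the document shows no prognostic value for it, and the likely gain is about 1% of the standard error or less.

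**Conclusion.** The point holds in a limited form. The total-episodes analysis leaves out sickle cell status and thalassaemia type, which the primary model includes, without a reason and although both are known from screening. This is a small inconsistency within one section. The haemoglobin comparison names no adjustment for a baseline that every child has.

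The cost is precision only. A reader might infer that the secondary results would be biased or their error rates inflated. Nothing in the protocol supports that: the omitted variables precede vaccination, allocation is random, and the primary analysis is already adjusted for five covariates.

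For haemoglobin the saving in variance is 9% to 49%, which rests wholly on the assumed correlation of 0.3 to 0.7. For episode counts the gain is unquantified. Severity is low.

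**What to change.** 1. For the total number of episodes, use the covariate set of the primary model: age, bed net use, blood stage immunity, sickle cell status and thalassaemia type. If the two traits are left out on purpose, give the reason.
2. Compare haemoglobin at three months and at the end of surveillance by ANCOVA, with screening haemoglobin and age as covariates. Sex may be added because it orders the allocation list, but this is optional.
3. Settle both in the protocol or in the reporting and analysis plan before the code is broken, so that no covariate is chosen with the results in view.

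The cost is a change of wording. No new data, samples or visits are needed, and the sample size is not affected.

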**10) Time Frame**

Pilot Study

Not applicable

Definitive study

Community sensitisation/recruiting Jan 2005

Screening 1 Feb- March 2005

1st immunisations March 7th-March 18th

Catch up immunisations March 21th-24th

2nd immunisations April 4-April 15th 2005

Catch up immunisations April 18th-April 22nd

3rd immunisations May 2nd-May 13th. 2005

Catch up immunisations May 16-20th

Surveillance May 16th – January 30th 2006

**11) Ethical Considerations**

The protocol will be submitted to both the KEMRI National Ethics Committee, and the Oxford Research Ethics Committee. Changes to the protocol requested by either committee will be referred to the other for approval. The Ethics Committees must be informed of serious and/or unexpected adverse experiences occurring during the study, and any new information that questions the safety of the subjects or the conduct of the study.

Human subjects

*Confidentiality*

All notes will be held securely in a filing cabinet in a locked office. Electronic databases will identify subjects by serial number only. For safe keeping, a second database linking serial numbers to personal information will be created at the end of the trial, and stored separately. This will ensure that rapid access to data should further follow up be required, and will allow passive monitoring of adverse events presenting to Kilifi District Hospital to continue after the end of the trial.

*Duty to minimise risks to children*

Adverse events are possible with any new vaccine. The risk is minimised by use of two candidate vectors chosen specifically for their good safety profile and their inability to replicate in humans. The comprehensive quality control, toxicology and manufacturing data to Good Manufacturing Practice and the absence of serious adverse events in phase I studies in Oxford and the Gambia, and phase 1 studies for adults and children in Kenya, provides firm evidence of the minimal nature of risk in this study. However anaphylaxis is estimated to occur at a frequency at 1 in 105 to 106 with all vaccines. Should this occur resuscitation facilities and appropriately trained personnel will be available to manage the reaction.

###### Duty to assure high standards of informed consent

We will provide detailed information about the study for distribution to parents. The principal investigator will ensure that all parents fully understand the risks. As with any experimental vaccine the parents must understand that they have not yet been shown to prevent infection and this will be stressed during the recruitment stage. They must also understand the very small chance of anaphylactic reactions and thereby the importance of complying with the one hour observation period after each vaccination. The information sheet (attached) covers these points in detail, and each parent will have attended a public meeting, had the contents of the sheet explained in individual meetings on 2 separate occasions, including a quiz/ comprehension test administered prior to signing the form. This process is similar to that used for Phase 1 studies (SCC protocol no 650) and we believe has produced a high standard of informed consent.

*Inducement*

We would not offer any financial incentive to attend. There will be a perception of benefit from physical examination, laboratory screening and aspects of routine care such as treatment of iron deficiency and vitamin A supplementation. Health screening, and the early detection of malaria have been perceived as benefits in other studies.

We do not feel that these are benefits excessive, and all could be routine community based health care. We would also provide the children with toys and books during the time they are required to be observed in the clinic.

Animal subjects

Not applicable

**12) Expected Application of Results**

The current failure of control measures, the difficulty of providing and maintaining bed nets, the rise in drug resistance to commonly available antimalarials and the increase in malaria attributable mortality over recent years argue strongly the need for a malaria vaccine. Demonstrating efficacy against disease in the field is a critical step in the path for vaccine development. Furthermore, the study of immunogenicity and it’s correlation with immunity will aid rational vaccine design to improve the product if this is required.

**14) Budget**

USD KSh

a) Personnel, salaries and benefits disbursement 200,000 14,000,000

b) Patient costs, travel, food and/or supplies 1,000 70,000

c) Equipment 10,000 700,000

d) Supplies 1,000 70,000

e) Travel and accommodation - local 1,000 70,000

- international 1,000 70,000

f) Transportation, vehicle repairs etc 25,000 1,750,000

g) Operating expenses postage, printing etc. 2,000 140,000

h) Animals acquisition etc. 0

i) Consultancy fees 0

j) Contingency fees (15% of above) 36,150 2,530,500

k) Institutional administrative overheads 0

**Total** 277,150 19,400,500

Supplementary Budget for further studies in Oxford

USD KSh

a) Personnel, salaries and benefits disbursement 7,900 528,000

b) Patient costs, travel, food and/or supplies 0 0

c) Equipment 0 0

d) Supplies 0 0

e) Travel and accommodation - local 0 0

- international 2,200 144,000

- shipping 1,200 71,400

f) Transportation, vehicle repairs etc 0 0

g) Operating expenses postage, printing etc. 0 0

h) Animals acquisition etc. 0

i) Consultancy fees 0

j) Contingency fees (15% of above) 1,500 100,000

k) Institutional administrative overheads 0

**Total** 12,700 844,400

**15) Justification of the Budget**

The study is part of the KEMRI-Wellcome Trust programme and will not incur any consultancy fees or additional administrative overheads. Costs for transport and field supplies are based on those incurred by projects of a similar size run in KEMRI-CGMRC. This will require 10 field workers, 10 motorbikes and running costs for a landrover.

